#### Recruitment strategies

Training will be provided to all individuals who can identify eligible participants for the study. These individuals will be contacted on a regular basis by the study co-ordination team to promote recruitment.

#### Loss of capacity to consent to research during participation in the study

It is possible that the stroke survivors recruited to this study may temporarily (e.g. because of intercurrent illness) or permanently (e.g. because of further stroke) lose the capacity to consent to this research project. In either case, it is unlikely that they will be able to continue to participate in a study which involves self-management. In the event of likely temporary incapacity, the intervention will be stopped whilst the participant is unwell, but restarted on recovery if the participant wishes to continue. In the event of permanent incapacity, the participant will be withdrawn from the study. Data collected prior to withdrawal will be retained and used in the study analysis as documented in the patient information sheet.

#### Healthcare professionals

Eligible healthcare professionals (HCPs) will be identified and approached by the study research team, a discussion about the study will be held, and the HCPs will be provided with an information sheet. After allowing sufficient time for this information to be considered, and an opportunity to ask questions, the study research team will obtain written consent from the HCPs.

The original consent forms will be retained at the study sites, and a copy will be given to the HCPs.

### Data collection

After consent, the following data will be collected to characterise the cohort and inform future studies:

#### Stroke survivors

Age (years); sex (male/female); pre-morbid walking status (independent/walks with an aid); marital status (single, married/remarried, separated, widowed, divorced); occupation pre-stroke (e.g. school teacher, retired); current work status (full-time paid, part-time paid, causal, registered sick/disabled, retired, unemployed, student); medical history (diabetes, arthritis etc.); geographical location (post code) education (year count); date of stroke; assistive device use (no device/stick/tripod/elbow crutches/zimmer frame/delta frame/four wheeled walker/wheelchair/other); Rivermead Mobility Index [27]; Fatigue Assessment Scale [28]; Warwick-Edinburgh Mental Well-being Scale (WEMWBS) [29]

#### HCP demographic information

Place of work, sex, occupation, years qualified, years specialising in stroke and employment status (whole-time equivalent)

### Stroke survivor intervention

#### Procedures

The stroke survivor intervention will target free-living physical activity and sedentary behaviour through a supported self-management programme. The supported self-management programme is underpinned by the Health Belief Model [30] and Self-Regulation Theory [31]. The following 17 behaviour change techniques (BCTs) have been incorporated into the programme: information about health consequences, salience of consequences, social support (unspecified), instruction on how to perform the behaviour, demonstration of the behaviour, goal setting (behaviour), problem solving, information about antecedents, monitoring of emotional consequences, information about health consequences, information about social and environmental consequences, social reward, habit formation, credible source, action planning, feedback on behaviour and self-monitoring of behaviour. These BCTs are used to target each construct of the behaviour change theories/models and thus aim to operationalise the models in order to target and change the target behaviours. The intervention will be supported by HCPs. The first face-to-face session/s the stroke survivor has with the HCP will consist of assessment of psychological well-being, fatigue and mobility using reliable and valid questionnaires. This will be followed by identification of preferred behavioural outcome, activity selection, personalised goal setting (behaviour and outcomes), action planning, barrier identification and coping planning (Fig. 1). The stroke survivor’s progress will then be reviewed by the HCP. The progress review session/s will be timed around the short-term goals (reviewed within less than three months) identified by the stroke survivors, e.g. if a goal is set for three weeks’ time, the review session will be delivered three weeks from when the goal was set. The review will focus on progress towards outcomes and behavioural goals. If goals have been achieved, maintenance or support to further progress goals will be provided. The overall aim of the intervention is to equip the stroke survivors with the knowledge and skills to enable them to self-manage their physical activity and sedentary behaviour in the long-term.

**Fig. 1 Fig1:**
[figure not shown]
Stroke survivor intervention programme

#### Materials

All stroke survivors will be provided with a paper-based workbook. The workbook contains questionnaires on psychological well-being, fatigue and mobility; information on the benefits/potential outcomes of moving more and sitting less; a list of potential activities, goal setting/action planning/barrier identification/coping planning and progress review sheets. Alongside the workbook, a number of tools will be used on an individual basis including pedometers and instructions, information on apps, physical activity diaries and wall planners and a repository of physical activity resources in the local area. For example, if a stroke survivor would like to increase their daily step count, they may be provided with a pedometer to enable self-monitoring of this activity, or if they wish to break up their sedentary time by standing every hour, they may be advised on a commercially available app that provides feedback on sitting time. The intervention materials that will be used on an individual basis are listed in Table 1 alongside their relationship to the theoretical constructs of the health behaviour change models used to underpin the programme and specific behaviour change techniques.

**Table 1 Tab1:** Intervention materials and their relationship to theoretical constructs and behaviour change techniques

Intervention programme materials	Form and information content	Theoretical constructs	Behaviour change techniques
Workbook	Paper-based workbook incorporating general advice on moving more and sitting less, self-assessment measures of well-being, fatigue and mobility, benefits of moving more and sitting less, potential outcomes list; physical activity options; goal setting; self-monitoring, action planning; barrier identification, progress review; example goal sheets	Health Belief model (HBM) Constructs: all constructs of HBM Self-regulation theory Constructs targeted: Individual perceptions; likelihood of action; goal setting; problem solving; self-monitoring; feedback	Information about health consequences Salience of consequences Social support (HCP) Instruction on how to perform a behaviour Goal setting Problem solving Information about antecedents Monitoring of emotional consequences Information about emotional consequences Information about social and environmental consequences Habit formation Action planning Feedback on behaviour Self-monitoring
Discussion cards	Laminated discussion cards with potential physical activity options and outcomes	Self-regulation theory Constructs targeted: action planning Health Belief Model Constructs targeted: Individual perceptions	Action planning
Summary sheet	Paper-based sheet with goals, action plans and coping plans	Self-regulation theory Constructs: action planning, goal setting, problem solving	Goal setting (behaviour) Action planning Problem solving
Physical activity self-monitoring tools	Participants will select a physical activity or sedentary behaviour self-monitoring tool from a range of options including: paper-based activity diary; laminated wall activity planner/diary; pedometer; commercially available physical activity monitoring apps	Self-regulation theory Constructs targeted: self-monitoring	Self-monitoring
Physical activity repository	Paper-based repository of locally based physical activity options and online resources	Self-regulation theory Constructs targeted: goal setting	Instruction on how to perform a behaviour Social support

#### Mode of delivery

The self-management intervention programme will be supported by HCPs (e.g. physiotherapists, occupational therapists, rehab assistants) working in community stroke teams. The HCPs will all have specialist knowledge in community stroke rehabilitation. The first session/s will be delivered face-to-face with review sessions delivered either face-to-face or by telephone.

The intervention programme will be initiated once the stroke survivor is moving towards supported self-management and a need to move more and sit less has been highlighted. The time from stroke will vary dependent on needs of the stroke survivor/health care professional’s opinion on the best timing/availability of resources. Participants may still be receiving rehabilitation from the community stroke teams at the same time as the delivery of the intervention.

#### Dose and duration

Stroke survivors will have contact with the trained HCP on at least two occasions. There is no upper limit to the number of HCP supported sessions/time to deliver sessions. The number of sessions will be defined by the stroke survivors’ support needs/availability of resources.

#### Tailoring

The intervention programme will be tailored to support the individual needs of the stroke survivors in relation to ability/preference and values.

### HCP training programme

#### Procedures

The behaviour of the HCPs in supporting stroke survivors to increase free-living physical activity/reduce sedentary behaviour will be targeted by a training programme consisting of face-to-face training with the research team, a training workbook and feedback on the delivery of the intervention.

#### Materials

The HCPs will be provided with a training workbook with activities to aid their development of knowledge and skills to support physical activity/reduce sedentary behaviour after stroke. The HCPs will also be provided with a repository of tools which will be used on an individual basis with stroke survivors (e.g. stroke survivor workbook, pedometers, pedometer instructions, discussion cards, physical activity information repository (see Table 1)).

#### Mode of delivery

The HCP training programme and fidelity assessment will be delivered face-to-face, by telephone and via email contact with members of the research team. The members of the research team who will be providing the training include an HEE/NIHR Clinical Lecturer stroke physiotherapist (qualified in physiotherapy for over 19 years, specialising in stroke for 14 years, specialising in stroke physical activity research for 10 years) and two health psychologists/senior researchers with extensive expertise in the development, evaluation and optimisation of lifestyle behavioural interventions for people with long-term conditions, including delivery of training to HCPs on the deliver behavioural interventions in clinical settings.

#### Dose and duration

The face-to-face training programme will last up to 4 h and be delivered to each community stroke team individually. The training will continue throughout the study through the use of the training workbook and feedback from the research team.

#### Tailoring

The HCP training programme will be tailored to the needs of each individual HCP through feedback on intervention delivery.

### Outcome assessments

#### Stroke survivors

At review sessions, the following outcome assessments will be reassessed: stroke survivor’s psychological well-being (Warwick-Edinburgh Mental Well-Being Scale [29]), fatigue (Fatigue Assessment Scale [28]) and mobility (Rivermead Mobility Index [27]). The number of times these measures are reassessed will be dependent on the number of review sessions they undertake with their healthcare professional.

#### Acceptability of the study intervention

A questionnaire with a combination of closed and open questions will be provided to each of the stroke survivors to gather their views of the intervention programme. Likert scales will be used to explore levels of agreement with different statements on acceptability of different aspects of the intervention, e.g. ‘I had good support from my healthcare professional during my participation in the PARAS study’, Additional comments on each statement and views on any aspect of the intervention that could be changed will allow further exploration of acceptability. Stroke survivors will be provided with a pre-paid envelope to return their questionnaires to the study team.

Alongside capturing the views of the stroke survivors via questionnaire, a sub-sample will be interviewed to determine acceptability of the intervention programme. Face-to-face semi-structured interviews of approximately 1 h will be undertaken. An estimated sample of up to 13 stroke survivors will be interviewed in line with published guidance for theory-based qualitative interview studies. Purposive sampling will be used to recruit stroke survivors who have completed the study. Purposive sampling has been chosen to ensure a maximum variation sample based on gender, age and stroke-related physical disability.

Potential participants will be invited to consent to being contacted to be interviewed during their initial consent to the study. Participants selected for interview will then be contacted either by telephone or by email and given a brief description of what the interview might address, such as how they felt about taking part in the study, engagement with the supported self-management programme and any impact they perceive on everyday activities.

### Healthcare professionals

#### Attitudes skills and reactions to training programme

The attitudes and skills of the HCPs pre- and post-training will be assessed via a questionnaire developed specifically for the study. The questionnaire has been piloted on the HCPs that undertook the pilot testing of the training programme and refined. A separate questionnaire will be used to establish HCP reactions to the training programme.

#### Acceptability of training programme and study protocol

The HCPs will be invited to attend a 2-h focus group at the end of the study to discuss their views on the study protocol. Topics to be covered in the focus group will include the impact/potential benefits of PARAS, feasibility of delivering the stroke survivor self-management programme within usual care, the usability of the intervention tools (e.g. workbook, pedometers and instructions) and the acceptability of the mode and form of the stroke survivor intervention delivery.

#### Cognitive and behavioural skills of the HCPs in response to training programme

Analysis of audio-recordings of face-to-face and review sessions with the HCP will be used to assess the cognitive and behavioural skills of the HCPs delivering the intervention programme. All face-to-face sessions delivered by HCPs with the stroke survivors will be audio recorded. Following published guidance, the content of 20–40% of these recorded sessions will then be analysed [32].

### Fidelity of intervention delivery

#### Fidelity strategies for the design of the study

HCPs involved in the study will have face-to-face training on the study protocol and the components of the stroke survivor intervention programme to standardise the delivery of the intervention. The community stroke team staffing resources will be mapped out before the study to ensure resources are adequate to deliver the intervention programme over the study period. Resource pre-planning will be undertaken in-case HCPs enrolled in the study leave during the period of study delivery.

#### Treatment fidelity strategies for monitoring and improving HCP training

Standardised face-to-face training will be delivered on the study protocol and intervention delivery to all HCPs with direct involvement in the study and to other members of the team who may be supporting the study. During the face-to-face HCP training sessions, the skill acquisition of the HCPs will be assessed to ensure they have adequate knowledge and skills to deliver the intervention. Those who do not have the adequate skills and knowledge will receive additional tailored feedback and training.

#### Treatment fidelity strategies for monitoring and improving delivery of stroke survivor intervention

In order to maximise HCPs’ skills delivering the intervention programme, the first two sessions they deliver with stroke survivors will be audio recorded by the HCPs themselves. The content of these audio-recorded sessions will be analysed by the research team using a fidelity checklist based upon the components of the stroke survivor intervention. Feedback on the delivery of the components of the intervention will then be provided by the research team before the HCPs see more participants. The HCPs will also have email/telephone contact with the research team to request further top-up training.

#### Treatment fidelity strategies for monitoring and improving receipt of stroke survivor intervention

The understanding and cognitive and behavioural skills of the stroke survivors undertaking the intervention programme will be checked by HCPs during face-to-face sessions by asking stroke survivors to independently complete a summary sheet of their goals, action and coping plans after they have completed their workbooks. The content of this summary sheet, use of intervention tools and analysis of audio-recorded sessions will also be used to monitor stroke survivor receipt of the intervention.

#### Treatment fidelity strategies for monitoring and improving enactment of stroke survivor skills

Completion of stroke survivor workbooks and use of intervention programme tools (e.g. physical activity diaries) will be checked at review sessions by HCPs to monitor stroke survivor self-management skills.

### Safety

The safety of the intervention will be evaluated by examining the occurrence of serious adverse events. This study will only report adverse events which are considered to be serious.

The standard definitions for serious adverse events will be used in this study:

*Serious adverse event (SAE)*: an untoward occurrence that:
Results in deathIs life-threatening (refers to an event in which the subject was at risk of death at the time of the event; it does not refer to an event which hypothetically might have caused death if it were more severe)Requires hospitalisation, or prolongation of existing hospitalisationResults in persistent or significant disability or incapacityIs otherwise considered medically significant by the investigator

Medical judgement will be exercised in deciding whether an adverse event is serious in other situations. Important medical events that are not immediately life-threatening or do not result in death or hospitalisation but may jeopardise the patient or may require intervention to prevent one of the other outcomes listed in the definition above should also be considered serious.

Serious adverse events *exclude*:
Pre-planned hospitalisationsScheduled treatment for pre-existing conditions.

Capture of potential SAEs will take place at face-to-face review sessions by including the following questions in the outcome pro forma: “are there any new medical problems since the last study visit?” For any events which fulfil the criteria to be a SAE and are unreported, the study SAE form will be completed.

Events considered to be SAEs will subsequently be documented onto a separate study SAE form, and a causality and expectedness assessment will be performed. As study investigators or other members of the research team may become aware of SAEs at times other than at review assessment appointments, the SAE form will also be used to directly capture these events.

Initial/provisional SAE reports can be made by telephone or email to the study co-ordinating centre. All initial/provisional reports must be followed by a fully completed SAE form. If incomplete information is available at the time of this initial report, further information must be provided on a follow-up form as soon as it is available. All SAEs regardless of causality or expectedness will be reported to the Chief Investigator and trial sponsor (Northumbria NHS Foundation Trust) in line with local policies. The main REC will be notified of related and unexpected SAEs within 15 days of the Chief Investigator becoming aware of the event.

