**Methods:**

This study will be set in community stroke services in the North East of England and will assess the feasibility of a behaviour change intervention targeting free-living physical activity and sedentary behaviour of stroke survivors *and* consultation behaviour of the healthcare professionals to support stroke survivors to make these lifestyle changes. Up to 35 stroke survivors currently receiving stroke rehabilitation within the study catchment area with capacity *and* no contraindications to increasing physical activity/reducing sedentary behaviour will be recruited. Stroke survivors will receive a supported self-management physical activity/sedentary behaviour programme incorporating provision of information, goal setting, action planning, barrier identification, coping planning, self-monitoring and feedback on physical activity and sedentary behaviour. The programme will be supported by up to 12 healthcare professionals (HCPs) recruited from the community stroke services taking part in the study. The HCPs will deliver at least two face-to-face sessions (baseline, review and subsequent reviews if necessary) and provide a range of personalised tools to support each individual stroke survivor (e.g. workbook, self-monitoring tools, information on local resources). The consultation behaviour of the HCPs will be targeted via a training programme incorporating face-to-face training, a training manual and individual feedback on intervention programme delivery from the study research team. The feasibility, acceptability and fidelity of the study protocol will be assessed.

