### Data analysis

#### Objective 1

Stroke survivor recruitment rate/month (total per site) and attrition rates/site and reasons will be described. HCP recruitment will be described as number of HCPs recruited compared to number of eligible HCPs in each team. Non-completion of training programme (e.g. face-to-face training, workbook, feedback) will be described as a percentage of non-completers out of the total of HCPs recruited.

#### Objective 2

The profession of the HCP delivering the intervention; the number and time taken (minutes) for face-to-face/telephone intervention delivery, the application of the different intervention components applied (e.g. self-monitoring tools, activity selection) and safety reporting will be described.

#### Objective 3

Completeness of outcome measure data collection including questionnaires will be described (number and percentage). Summary descriptive statistics (e.g. mean and standard deviation, median and interquartile range, 95% confidence interval as appropriate) will be used to describe stroke survivor baseline demographics and psychological well-being (Warwick-Edinburgh Mental Well-Being Scale), fatigue (Fatigue Assessment Scale) and mobility (Rivermead Mobility Assessment) at baseline and review.

#### Objective 4

Closed questionnaire data from stroke survivors will be coded and summarised. Open-ended questions have also been included in order to encourage full, meaningful answers using the participants own words that might potentially offer insights or issues not captured in the closed questions, yielding more accurate information to inform future studies. Answers to open questions will be thematically explored in order to identify, analyse and report patterns (themes) within the data.

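### The serious adverse event question is tied to face-to-face reviews although reviews may be by telephone, so ascertainment is uneven and a low count would be hard to interpret

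*Protocol article*

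**What the plan says.** All references are to the protocol article.

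- **Safety**, solicited route: "Capture of potential SAEs will take place at face-to-face review sessions". The means is a question in the outcome pro forma about new medical problems since the previous study visit.
- **Safety**, unsolicited route: the team may learn of SAEs outside review appointments, and "the SAE form will also be used to directly capture these events".
- **Safety**, scope: "This study will only report adverse events which are considered to be serious".
- **Stroke survivor intervention, Mode of delivery**: "The first session/s will be delivered face-to-face with review sessions delivered either face-to-face or by telephone".
- **Stroke survivor intervention, Dose and duration**: "Stroke survivors will have contact with the trained HCP on at least two occasions". The mode of these contacts is not given.
- **Abstract, Methods**: "The HCPs will deliver at least two face-to-face sessions (baseline, review and subsequent reviews if necessary", so at least one review would be face-to-face.
- **Data analysis, Objective 2**: the description will cover "the number and time taken (minutes) for face-to-face/telephone intervention delivery", together with safety reporting. Telephone delivery is thus expected to occur.

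**The concern.** Safety is a named part of Objective 2, and the Safety section evaluates it by the occurrence of SAEs. The only planned question that looks for SAEs is attached to one mode of review, while the Methods allow two. Whether a participant is asked then depends on how the review was arranged and on whether a review took place.

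The second dependence may be related to the outcome. The Study withdrawal section lets clinical teams withdraw a participant for intercurrent illness. The section on loss of capacity withdraws those permanently incapacitated, with further stroke as its example. Neither attaches an SAE question to that point. If such participants leave before a review, some of those most relevant to safety go unasked. With at most 35 stroke survivors, a handful of unasked participants changes what a count of zero or one means.

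**Working it through.** The article gives no expected SAE rate, no target precision for safety and no formal sample size calculation. There is no stated figure to reproduce, so the main check is textual.

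**Step 1. Follow a participant through the sections.**

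| Path | Governing text | Asked the SAE question? |
|---|---|---|
| Face-to-face first session, face-to-face review | Abstract, or Mode of delivery | Yes |
| Face-to-face first session, one telephone review, no more contacts | Mode of delivery with Dose and duration | No, as Safety is written |
| Telephone review, then a later face-to-face review | Mode of delivery | Yes, at the later review |
| Withdrawn before any review | Study withdrawal | No |

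The second path meets the two-contact minimum, so a participant can complete the Methods without being asked. Under the Abstract that path does not exist, because a review must be face-to-face. The two descriptions cannot both govern.

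**Step 2. Allow for the unsolicited route.** Let t be the share of participants reviewed only by telephone or not at all, and c the chance that the unsolicited route finds an SAE in such a participant. Assuming full capture among those asked face-to-face and the same SAE risk in both groups:

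share of SAEs captured = (1 − t) + t × c

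The article gives neither t nor c, so a range is shown.

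| t | c = 0 | c = 0.5 | c = 0.8 | c = 1 |
|---|---|---|---|---|
| 25% | 75% | 87.5% | 95% | 100% |
| 50% | 50% | 75% | 90% | 100% |
| 75% | 25% | 62.5% | 85% | 100% |

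Example: t = 50%, c = 0.5 gives 0.5 + 0.5 × 0.5 = 0.75. Capture is incomplete whenever t > 0 and c < 1. Nothing is captured from the unasked group only if c = 0, which the Safety section does not imply.

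**Step 3. What a count of zero would mean.** With zero events in n participants, the exact one-sided 95% upper limit solves (1 − p)^n = 0.05, so p = 1 − 0.05^(1/n).

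| Number asked, n | Share of 35 not asked | Upper limit |
|---|---|---|
| 35 (planned maximum) | 0 | 1 − 0.05^(1/35) = 8.2% |
| 26 (assumed) | 9/35 = 26% | 1 − 0.05^(1/26) = 10.9% |
| 18 (assumed) | 17/35 = 49% | 1 − 0.05^(1/18) = 15.3% |
| 9 (assumed) | 26/35 = 74% | 1 − 0.05^(1/9) = 28.3% |

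These limits apply to those asked and give the unsolicited route no credit. The protocol plans no such bound; they only show how far the reading of a zero depends on a denominator that the plan does not say it will report.

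**The case against.** The case on the other side has real weight.

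- **The unsolicited route.** Delivery is by community stroke teams, who may still be treating the participant, and they have other ways of hearing of a death or admission. A reason is sought at withdrawal, and reasons for attrition are described. This stands: SAEs in unasked participants may be under-ascertained, but a reader should not infer that they are all missed. The route has no question, contact or time point attached, however, so its yield is unknown. The telephone and email provisions concern reporting an SAE already known, not finding one.
- **The question looks back.** An event before a telephone review can be picked up at a later face-to-face review, provided the call is not itself counted as the last study visit. This limits the main gap to participants with no face-to-face review.
- **The Abstract may govern.** If so, everyone who completes the minimum is asked at least once, and most of the gap closes. That is a reason to reconcile the text, because the Methods say otherwise.
- **Practice may be better than the text.** The question sits in the outcome pro forma, and the Outcome assessments section reassesses outcomes at review sessions without naming a mode. A fuller protocol or telephone script may also exist. But the Safety section states a rule and confines it to face-to-face reviews; the point rests on that rule, not on an omission.
- **Little hangs on the count.** No progression criterion refers to SAEs, and Objective 2 is descriptive. This lowers the stakes, but a descriptive count still needs a known denominator.

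**Conclusion.** The point holds as an inconsistency that makes SAE ascertainment depend on review mode. Under Mode of delivery and Dose and duration, participants reviewed only by telephone or withdrawn before review are never asked, and a low SAE count would be hard to interpret. The size cannot be fixed from the article: it could be close to nil if the Abstract governs or the unsolicited route works well, and large if telephone-only review is common and that route finds little.

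Two stronger readings are not supported. A reader might infer that the safety objective cannot be met. Objective 2 only asks for safety to be described, and the Safety section defines it by SAEs, so it can be met with imperfect ascertainment, if less informatively. A reader might also object that non-serious falls go unreported in an intervention that asks people to move more. Reporting only serious events is a declared choice of scope, not a contradiction. Falls are not mentioned in the article, and one that the investigator judged medically significant would qualify as an SAE.

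**What to change.** 1. Reconcile the Abstract, Mode of delivery and Safety sections on whether a review must be face-to-face. Which mode is required is for the investigators to settle.
2. Whatever is settled, ask the existing question about new medical problems at every review contact, by telephone or face-to-face.
3. Ask it also when the reason for withdrawal is sought. Participants may decline, as they already may for the reason itself.
4. Report the number of participants actually asked as the denominator beside the SAE count.

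The cost is slightly more healthcare professional time per telephone review and at withdrawal, and one extra number in the report. No new instrument or visit is needed.
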